#### Randomisation process

The enrolment/randomisation process has been successfully tested in the previous pilot study. Randomisation will be achieved by an opaque envelope in sequential order with an allocated infant ratio of 1:1. A computer-based randomisation will be used to allocate infants 1:1 per site. Randomisation can occur at admission or at any time during hospital stay when an oxygen requirement develops.

### Treatment arms

#### Control

The infant that is randomised to the Control arm will be placed on standard subnasal cannula with oxygen flows up to a maximum of 2L/min according to local hospital practice to maintain SpO2 between 92-98 % (94-98 %). This may or may not be humidified oxygen, and will be according to current individual hospital guidelines. Oxygen flows should be administered below 2L/min to commence with and increased as required to maintain SpO2 ≥ 92 % (≥ 94 %).

#### HFNC therapy

The infant that is randomised to the HFNC therapy arm with SpO2 85-91 % (85-93 %) will be placed on high flow at 2L/kg/min (up to a maximum of 25 L/min) in room air equating to a fraction of inspired oxygen of 21 % (FiO2). They will remain on room air for a minimum of 10 minutes whilst monitoring SpO2. If SpO2 starts to increase and stabilise at ≥92 % (≥94 %) then continue on room air of 21 %. If SpO2 has not altered or improved then the FiO2 will be slowly increased to maintain SpO2 ≥ 92 % (≥94 %). The infant that is randomised to the HFNC therapy arm with SpO2 < 85 % will commence on high flow with FiO2 slowly increasing to achieve SpO2 ≥ 92 % (≥94 %).

#### Other interventions/therapies/nutrition

The use of any medications such as steroids, antibiotics, antipyretics, bronchodilators and hypertonic saline is at the discretion of the attending clinicians and not prescribed in the protocol. These interventions will be recorded in the clinical research form (CRF). Feeding in standard subnasal cannula oxygen therapy is not prescribed and clinicians can choose to administer continuous or bolus feeds or use intravenous fluids. However, in the HFNC therapy intervention arm a nasogastric tube will be inserted, the stomach must be vented at 4 hour intervals, and no oral feeding will be allowed unless in stable weaning phase. Feeding rate should be prescribed as per individual hospital policy using nasogastric (bolus or continuous feeds).

The nursing ratio for both arms will remain according to the standard current ward management already present and as per usual hospital protocol. The nurse/patient ratio is important to maintain, to ensure that infants with the same level of illness do not get increased nursing care due to being on one type of therapy over another. Clinical documentation will be achieved according to individual hospital standards. Admission criteria to intensive care and triggering of medical review (use of early warning tool) will also follow individual hospital rules.

#### Choice of 2L/kg/min flow rate

Studies have demonstrated that the maximal inspiratory flow that a healthy infant achieves during regular breathing is 0.8 L/kg/min for each breath. An unwell infant such as an infant with bronchiolitis, generates a higher inspiratory flow which can be as high as 1.0-1.6 L/kg/min [10, 23]. The aim of HFNC therapy is to match this maximal inspiratory flow generated by the infant, so that no additional air is entrained around the nasal prongs. For this purpose a safety margin of 2 L/kg/min is given, to ensure adequate flow is provided for these infants.

There is a population of larger babies less than 12 months of age and the HFNC therapy for this study will not exceed 25L/min. This is based on using the infant’s ideal weight rather than actual weight as a measure of how to deliver the flow for the larger babies.

#### Weaning

Responders in the *standard subnasal oxygen therapy arm* will be weaned from 2 L/min or less if SpO2 remains stable at 92-98 % (94-98 %). Infants will be weaned to room air and nasal cannula removed once an infant is able to maintain saturations in the target range on room air for at least four hours. SpO2 to be maintained within 92-98 % (94-98 %) at all times and if <92 % (<94 %), then oxygen flow will increase again until SpO2 within 92-98 % (94-98 %). Once SpO2 is stabilised, weaning will recommence, using the same parameters.

For responders in the *HFNC therapy arm*, flow rates will be kept at 2L/kg/min, while FiO2 is decreased. Flow rates are *not* to be weaned and are to be maintained at 2L/kg/min until HFNC therapy is ceased and turned off completely. Once FiO2 has reached 21 % with SpO2 maintained between 92-98 % (94-98 %) for four hours the high flow off is turned off and the nasal cannula are removed.

#### Escalation of therapy after treatment failure (primary outcome)

Once failure criteria are met, escalation of treatment may be from standard subnasal oxygen therapy to HFNC therapy and/or escalation to non-invasive ventilation or intubation and mechanical ventilation in intensive care. It is at the discretion of the attending physician to manage and treat the ongoing care. If escalation from standard subnasal oxygen to HFNC therapy occurs then the same protocol shall be applied as in HFNC therapy arm. However, at any time during the study the physician can override and escalate care. This aspect of clinical reasoning to escalate will be captured in the data set and is defined as follows: i.) increased work of breathing requiring escalation of respiratory support, ii.) decreased conscious level, iii.) deterioration of cardiovascular function with impaired peripheral perfusion, iv.) clinical judgment of attending (senior) medical officer triggers escalation of treatment and care.

With any escalation of treatment the nurse/patient ratio will be captured to perform cost assessments on required level of care at the time of escalation and thereafter.

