## Methods

### Study aims

To perform a randomised controlled multicentre trial (RCT) in infants aged less than 12 months (corrected age) with clinically diagnosed bronchiolitis comparing HFNC therapy to standard subnasal oxygen therapy. The primary outcome is treatment failure of HFNC therapy or standard subnasal oxygen.

Secondary outcome measures comprise (a) the rate of transfer of children to higher level care (that is, the rate of transfer from regional hospitals to tertiary centres and rate of transfer from tertiary hospitals to their onsite intensive care unit (ICU) if the primary admission is to their tertiary hospital); (b) length of stay in hospital and (c) health care costs associated with the therapy, transfer and ICU admission (including intubation rates), and overall length of stay; (d) length of oxygen therapy; (e) and measurement of adverse side effects. We hypothesise that HFNC therapy will have a lower failure proportion, reduced transfer rate, reduced length of stay, and lower health care costs associated with the treatment, in comparison to standard subnasal oxygen.

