#### Setting

Emergency departments and general paediatric wards of 17 hospitals in Australia and New Zealand, including 12 non-tertiary regional/metropolitan and 5 tertiary centres. Eight hospitals will have access to on-site intensive care units that cater for infants less than 12 months of age. Patients will be recruited in both the ED and general paediatric wards of these hospitals.

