### Primary outcome definition

The primary outcome is the proportion of infants in each group with treatment failure. Treatment failure of either standard subnasal oxygen or HFNC therapy arm is defined as meeting three out of four specified failure criteria requiring escalation of treatment or higher level of care such as high acuity or intensive care. Prior to escalation of care 2 to 3 hours of observing the infant in an undisturbed environment is suggested. This time frame was based on the pilot study whereby it was clearly identified that the infants who are going to fail will do so within 2 to 3 hours [12]. In the pilot study, those who failed HFNC therapy had unchanged or increasing heart rate and respiratory rate, or worsening SpO2. Clinicians are asked to wait 2 to 3 hours prior to escalation of care, however, if they are more concerned, their clinical judgement can override the protocol if a decision is made to escalate care.

***Treatment failure*** of either standard subnasal oxygen or HFNC therapy arm is defined if three of the four following criteria are met and an escalation of treatment or level of care is requiredheart rate remains unchanged or increased compared to admission/enrolment observations,respiratory rate remains unchanged or increased compared to admission/enrolment observations,oxygen requirement in HFNC therapy arm exceeds FiO_2_ ≥ 40 % to maintain SpO_2_ ≥ 92 % (or ≥94 %) or oxygen requirement in standard subnasal oxygen therapy arm exceeds >2L/min to maintain SpO_2_ ≥ 92 % (or ≥94 %)hospital internal Early Warning Tool calls for medical review and escalation of care.

The study design utilises a ***composite primary end-point of treatment failure***, which has previously been used in a RCT of HFNC therapy vs. CPAP post extubation in neonates conducted in Australia [22].

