### Secondary outcome definition

Secondary outcomes are defined as (a) the proportion of infants requiring transfer to higher acuity care, which includes admission to an on-site paediatric intensive care or transfer to a tertiary hospital; (b) length of hospital stay, including intensive care length of stay and (c) intubation rates; (e) associated health care costs for the respective therapy; (f) length of oxygen therapy and; (g) adverse events.

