### Sample size, power and statistical methods

#### Sample size

In 2011 there were 478 eligible patients admitted to 4 of 8 pilot hospitals (Queensland), of which 80 required transfer to a tertiary paediatric centre (16.7 %). Assuming a conservative baseline rate of failure of standard therapy (need for transfer to a specialist paediatric centre or PICU admission) of 10 %, a 50 % relative reduction to 5 % with a power of 90 % and type I error of 0.05, 582 participants per group are required, resulting in a total sample size of 1164 patients. An attrition rate of approximately 10-20 % is estimated, which gives an overall sample size of 1400.

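### The escalation that completes treatment failure is not the same event in both arms, so a significant primary result alone cannot show less need for higher-level care

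*Protocol article*

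**What the plan says.** Under Primary outcome definition, failure is declared in either arm if "three of the four following criteria are met and an escalation of treatment or level of care is" required. Escalation is thus a necessary part of the outcome. The criteria are heart rate, respiratory rate, oxygen requirement and a call from the hospital's early warning tool. All but the oxygen criterion are worded the same for both arms; that one uses an inspired oxygen fraction for HFNC and a flow rate for control.

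Under Escalation of therapy after treatment failure, "escalation of treatment may be from standard subnasal oxygen therapy to HFNC therapy and/or escalation to non-invasive ventilation or intubation and mechanical ventilation". Rescue HFNC follows the HFNC-arm protocol. Management after failure is at the physician's discretion, and the physician may override and escalate at any time. The Design section describes an open-label trial, and Limitations accepts that the endpoints can be seen as subjective.

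The sample size rests on another event: "Assuming a conservative baseline rate of failure of standard therapy (need for transfer to a specialist paediatric centre or PICU admission) of 10"%, and then "a 50 % relative reduction to 5 % with a power of 90 % and type I error of 0.05, 582 participants per group are required".

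Transfer or ICU admission is a secondary outcome with two descriptions. Study aims counts, besides transfers from regional hospitals to tertiary centres, the "rate of transfer from tertiary hospitals to their onsite intensive care unit (ICU) if the primary admission is to their tertiary hospital". Secondary outcome definition counts higher-acuity care "which includes admission to an on-site paediatric intensive care or transfer to a tertiary hospital". Setting says that "Eight hospitals will have access to on-site intensive care units that cater for infants less than 12 months of age" and gives five tertiary centres; Definitions speaks of six.

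**The concern.** A control infant who meets three criteria can be counted as a failure by being given the experimental treatment. The trial delivers that treatment in emergency departments and general wards, so this step need not involve intensive care. An HFNC infant who meets three criteria has already used it. What the text leaves for that infant is non-invasive ventilation, intubation, or a higher level of care such as high acuity or intensive care. If unblinded clinicians start HFNC more readily than they move an infant to heavier support, the control arm will collect more failures even when the disease course is the same.

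What is at stake is the reading of a positive result. It could mean that early HFNC prevents deterioration, that HFNC is easier to start than the next step up, or some of both. The primary outcome alone cannot separate these. The outcome closer to the same event in both arms, ICU admission or transfer, is described in two ways that disagree.

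**Working it through.** **1. The plan's own figure.** Inputs from Sample size: 10% against 5%, power 90%, type I error 0.05 (taken as two-sided). With pooled variance under the null and no continuity correction,

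n = [1.960·√(2p̄(1−p̄)) + 1.282·√(p₁(1−p₁)+p₂(1−p₂))]² / (p₁−p₂)²

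with p̄ = 0.075: (0.7301 + 0.4752)² / 0.0025 = 581.1, rounded up to 582. This matches. The total of 1164 grows to 1164/0.9 = 1294 at 10% attrition and 1164/0.8 = 1455 at 20%; 1400 corresponds to 16.9%, inside the stated range. The arithmetic is right for its inputs. Those inputs describe transfer or PICU admission, and a control infant who only moves to ward HFNC does not meet that description but can meet the primary outcome.

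**2. How much a difference in escalation could matter.** The documents do not give the share of infants meeting three criteria or the share of those escalated. Assumptions:
- HFNC has no effect, so the same share m meets the criteria in both arms.
- All such control infants are escalated, and a fraction r of such HFNC infants.
- Failure rates are therefore m and m·r.

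The chance of a significant result favouring HFNC is Φ[(d − 1.960·SE₀)/SE₁], where d = m − m·r, SE₀ = √(2p̄(1−p̄)/n) and SE₁ = √((p₁(1−p₁)+p₂(1−p₂))/n).

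Example, m = 10%, r = 0.8, n = 582: d = 0.02, SE₀ = 0.01678, SE₁ = 0.01677, so Φ(−0.768) = 0.22.

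| m | r | Control v HFNC | n = 582 | n = 700 |
|---|---|---|---|---|
| 10% | 1.0 | 10% v 10% | 2.5% | 2.5% |
| 10% | 0.9 | 10% v 9% | 8% | 9% |
| 10% | 0.8 | 10% v 8% | 22% | 26% |
| 10% | 0.7 | 10% v 7% | 45% | 52% |
| 15% | 0.9 | 15% v 13.5% | 11% | 12% |
| 15% | 0.8 | 15% v 12% | 32% | 38% |
| 15% | 0.7 | 15% v 10.5% | 63% | 71% |

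The benchmark is 2.5%, because only the tail favouring HFNC counts as a false benefit.

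**3. The same point on the additive scale.** Suppose escalation beyond HFNC occurs in 5% of each arm, and a further h of control infants meet the criteria and step up only to HFNC. At 582 per arm the chance of a significant result favouring HFNC is 11% for h = 1 point, 30% for 2 points, 55% for 3 points and 90% for 5 points. The last case gives 10% against 5%, the whole planned contrast.

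**4. The secondary outcome, side by side.** An infant admitted to an on-site ICU at a non-tertiary hospital falls within Secondary outcome definition but outside the wording in Study aims. With eight ICU hospitals, at least 8 − 5 = 3 of them are non-tertiary on the count in Setting, or 8 − 6 = 2 on the count in Definitions.

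**The case against.** Failure of first-line therapy with HFNC as the rescue is a coherent question. The Discussion states the aim as preventing treatment failure and escalation of respiratory support, and Study aims makes reduced transfer a separate hypothesis with its own outcome. This stands, and it is why the primary should be kept.

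A reader might infer that HFNC is set up to win whatever it does to the disease. The documents do not support that. Escalation alone is not failure: three criteria must also be met, and three of the four are worded identically by arm. Control infants may go straight to ventilation, so the escalation events overlap. The protocol does not say that rescue HFNC stays on the ward. Starting it brings a nasogastric tube and restricted oral feeding, so it is not a free step. The lower threshold in control is an inference from the wording and setting. These points limit the bias. They do not remove it, because the escalation component is required, discretionary and unblinded. Limitations admits subjectivity but not that the next step differs by arm.

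A reader might also infer that 582 per arm gives ICU admission or transfer 90% power. Nothing shows that 10% against 5% allows for control infants rescued with HFNC, which may shrink that contrast.

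Finally, ranking of secondaries, breakdowns and sensitivity analyses usually belong in an analysis plan, which is not shown. Their absence here is not the complaint. The complaint is that the article fixes an outcome with an arm-dependent component and describes the more comparable outcome in two conflicting ways.

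**Conclusion.** The concern holds as a limit on what the primary outcome can show. The escalation component differs by arm, and nothing in the article neutralises that. A significant primary could partly reflect readiness to start HFNC, and by itself it would not show less need for higher-level care.

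The size is unknown. Under the stated assumptions, at 582 per arm, the chance of a false result in favour of HFNC runs from 8% to 63% rather than 2.5%. It is at the low end if the escalation shares differ by only a tenth, and there is no inflation if they are equal. The rates of 10% and 15% and the escalation fractions are assumptions; the 10% only borrows the planning rate for a different event. The sample size calculation itself is correct. The conflict between the two descriptions of ICU admission or transfer is on the page and needs no assumption.

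**What to change.** Keep the primary outcome and the sample size. Before anyone sees outcomes by arm:

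1. Reconcile Study aims with Secondary outcome definition into one outcome, ICU admission or transfer, covering every site with an on-site ICU, and settle whether there are five or six tertiary centres. Name it the key secondary, tested at 0.05 only after a significant primary, and rest any claim of reduced higher-level care on it. State that it compares immediate HFNC with oxygen plus HFNC rescue, and that rescue may dilute the difference.
2. Report the primary by type of escalation in each arm, with a sensitivity analysis that counts only escalation beyond HFNC in both arms.
3. If early warning calls are recorded (Clinical observations does not list them, and the case report form is not shown), add a sensitivity analysis of infants meeting three of four criteria whether or not they were escalated. Note that the oxygen criterion still differs by arm.

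These change definitions and analysis only; no clinical escalation rule is proposed. The cost is a little more analysis, and the claim on higher-level care becomes conditional on the key secondary.

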#### Clinical observations

SpO2 will be measured at enrolment in room air. If the infant has had oxygen administered in the ambulance, then it will be ceased and SpO2 assessed a few minutes later to ascertain if the infant meets the inclusion criteria of SpO2 < 92 % (<94 %). Once this inclusion criteria has been established, respiratory rate, respiratory effort and heart rate will be measured at enrolment. Observations thereafter will be according to current hospital protocol within either the ED or general paediatric ward.

At each set of observations, the following parameters will be documented: SpO2, heart rate, respiratory rate, respiratory effort, oxygen/FiO2 administered, flow rate of high flow therapy and at frequent intervals the temperature and blood pressure will be monitored according to standard hospital guidelines.

Complications recorded will include episodes of apnoea and bradycardia (lasting more than 20 seconds); all episodes where the SpO2 was recorded <92 % (94 %) and adverse outcomes such as pneumothoraces or deaths.

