### Definitions

All infants aged 0-12 months with symptoms of bronchiolitis (as defined by the American Academy of Pediatrics) - symptoms and signs of respiratory distress and oxygen requirements are eligible [18]. Bronchiolitis is defined as signs and symptoms of respiratory distress associated with symptoms of a viral respiratory tract infection (cough, runny nose, blocked nose, tachypnoea, recessions, nasal flaring, and cyanosis) [3]. Oxygen requirement in room air is defined according to the World Health Organisation recommendation, if transcutaneous haemoglobin oxygen saturation (SpO_2_) is <94 % in room air [19–21]. Six participating tertiary centres in our study have a lower threshold of < 92 % as their standard practice of care. In these sites a threshold of < 92 % was accepted in the randomised design, different saturation thresholds in different centres will be balanced through randomisation across all sites.

***Inclusion criteria*** are infants with a clinical diagnosis of bronchiolitis less than 12 months corrected age (≥ 37 weeks post-conceptional age) with an oxygen requirement in room air of SpO2 < 92 % for tertiary centres and <94 % for regional and metropolitan centres.

***Exclusion criteria*** include those infants with urgent need for respiratory support ( i.e. non-invasive or invasive ventilation or low level of consciousness, apnoea), cyanotic heart disease, basilar skull fracture, upper airway obstruction, craniofacial malformations and infants who are already on home oxygen therapy.

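### Desaturation complications use the entry SpO2 threshold with no start time, so the HFNC room-air hold can inflate that arm's adverse-event count

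*Protocol article*

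**What the plan says.** All places are in the protocol article.

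- **Entry (Definitions).** Infants qualify with an "oxygen requirement in room air of SpO2 < 92 % for tertiary centres and <94 % for regional and metropolitan centres".
- **Complications (Clinical observations).** The list includes "all episodes where the SpO2 was recorded <92 % (94" (per cent). The only duration qualifier in the list belongs to other events: "episodes of apnoea and bradycardia (lasting more than 20 seconds" is how those are described. Desaturation has no start time, no minimum duration and no definition of a new episode. The frequency of observations is left to each hospital.
- **HFNC start (HFNC therapy).** Infants at 85-91% (85-93%) begin high flow "in room air equating to a fraction of inspired oxygen of 21 % (FiO2". The section then says: "They will remain on room air for a minimum of 10 minutes whilst monitoring SpO2". They stay at 21% only if SpO2 reaches target; otherwise FiO2 is raised to the same target as in control. Infants below 85% have no room-air hold.
- **Control start (Control).** The infant "will be placed on standard subnasal cannula with oxygen flows up to a maximum of 2L/min", starting lower and increasing as needed to hold the target.
- **Stopping (Weaning).** In HFNC the device comes off "Once FiO2 has reached 21 % with SpO2 maintained between 92-98 % (94-98 %) for four hours". In control the cannula comes off after four hours in target on room air.
- **Outcomes (Secondary outcome definition).** "length of oxygen therapy" and adverse events are both listed. Desaturation is not listed separately.

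**The concern.** The value that makes an infant eligible is the value that counts as a complication, so every infant starts treatment in the state being counted. The two arms leave that state under different rules. Most HFNC infants may be kept without added oxygen for a monitored period, and controls have no such period. Randomisation balances the infants but not this exposure. A reading that shows only that the presenting hypoxia has not yet resolved would enter the HFNC adverse-event count more often.

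At stake is the safety comparison. Adverse events are a secondary outcome, and the Discussion promises new information on the adverse-event profile of HFNC outside intensive care. An excess of desaturation produced by the start-up rule could be read as harm.

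A lesser point concerns oxygen duration. HFNC can be delivered at 21%, so time on the device and time on supplemental oxygen are different quantities, and the article does not say which is meant.

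**Working it through.** **1. The plan's own figure.** The article gives no rate for desaturation or oxygen duration. Its only calculation is for the primary outcome (10% versus 5%, 90% power, type I error 0.05). It is reproduced here because its group size is used below:

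n = [1.960·√(2·0.075·0.925) + 1.2816·√(0.10·0.90 + 0.05·0.95)]² / 0.05² = (0.7301 + 0.4752)² / 0.0025 ≈ 581.1, rounded up to 582 per group.

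This matches the stated 582. The point does not rest on it.

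**2. The start-up rules side by side.**

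| | HFNC, 85-91% (85-93%) | HFNC, below 85% | Control |
|---|---|---|---|
| SpO2 at entry | below complication threshold | below | below |
| Added oxygen at start | none for at least 10 min | yes, increased slowly | yes, increased as needed |
| Monitoring called for in that period | yes | local practice | local practice |
| Early low reading possible | yes | yes | yes |

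Early low readings are possible everywhere. Only the first column has a prescribed, monitored period without added oxygen, so the expected tilt is towards more charted episodes on HFNC.

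**3. Size, as an illustration.** None of these inputs is in the documents:

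- q: probability of at least one later recorded episode, the same in both arms (no true difference): 0.3 or 0.5
- s: share of HFNC infants in the hold band: 0.80 or 0.95
- a: probability that such an infant has a low reading charted during the hold that would not have been charted under control: 0.10, 0.25 or 0.50

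If early charting is independent of later episodes, p(HFNC) = 1 − (1 − q)(1 − a·s), so the excess is (1 − q)·a·s.

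- Smallest: (1 − 0.5) × 0.10 × 0.80 = 0.04
- Largest: (1 − 0.3) × 0.50 × 0.95 = 0.33

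The chance of a significant two-sided result at 0.05 with 582 per group is Φ{[d − 1.96·√(2p̄(1 − p̄)/n)] / √[(p₁(1 − p₁) + p₂(1 − p₂))/n]}, where d is the excess. For the smallest case (0.54 versus 0.50): (0.04 − 0.0574)/0.0293 = −0.59, giving 28%.

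| a | Excess, percentage points | Chance of a significant result |
|---|---|---|
| 0 | 0 | 5% (nominal) |
| 0.10 | 4.0 to 6.7 | 28% to 67% |
| 0.25 | 10.0 to 16.6 | 93% or more |
| 0.50 | 20.0 to 33.3 | above 99% |

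The result turns on a, which depends on how often each hospital charts.

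**4. Oxygen duration, as an illustration.** Suppose the time to cannula removal, T, is equal in both arms, with a four-hour period at 21% or on room air at the end of each. Let r be the share of HFNC infants at 21% throughout (0 to 0.4). The others are taken to receive supplemental oxygen until T − 4; the initial hold is ignored.

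| Counting rule | T = 24 h: HFNC / control | T = 48 h: HFNC / control |
|---|---|---|
| Device time in both arms | 24 / 24 | 48 / 48 |
| Supplemental oxygen in both: (1 − r)(T − 4) / (T − 4) | 12-20 / 20 | 26.4-44 / 44 |
| Mixed: supplemental in HFNC, cannula time in control | 12-20 / 24 | 26.4-44 / 48 |

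Only the mixed rule gives a difference when r = 0, and that difference is the four-hour period dropped from one arm. Under a single rule, any difference comes from r, which depends on the infant's response.

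**The case against.** **Desaturation.** It is a recorded complication, not a named secondary comparison, and no test of it is specified. Start times and tabulation are often settled in a full protocol or analysis plan that is not shown. The article also does not say that persisting presenting hypoxia is a new episode, and a careful site might not log it as one. These points limit the size and prominence of the problem. They do not remove it: the article states an all-inclusive rule, gives a duration qualifier to the neighbouring events and none to this one, and that rule sits badly with the HFNC start-up.

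A reader might infer that early low readings count against HFNC only. They do not. Controls also enter below threshold and are titrated upwards, and HFNC infants below 85% have no hold. A reader might also take half of the planned 1400, that is 700 infants, as the number affected. That would need full enrolment, every HFNC infant in the hold band, and every hold reading logged as a complication; the documents support none of these.

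**Oxygen duration.** Here the objection largely succeeds. A reader might infer that both outcomes are biased by construction, or that device time penalises HFNC by four hours. The Weaning section gives both arms a four-hour period at 21% or on room air before the cannula is removed, so device time carries no built-in penalty. Staying at 21% depends on reaching target, and needing less oxygen under flow is partly a real effect of the allocated strategy, which the intention-to-treat contrast properly captures. What stands is that the measure is not like-for-like until one counting rule is stated.

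**Conclusion.** The point holds for desaturation. The stated rule, with the entry threshold as event threshold and no start time, combines with a room-air hold in one arm only to tilt the complication count against HFNC. The direction follows from the text. The size is not in the documents and depends on local charting. Under the assumed ranges the spurious excess runs from 4 to 33 percentage points, and it is zero if the hold adds no charted readings.

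For oxygen duration the conclusion is weaker: an ambiguous measure, with neither the existence nor the direction of a bias established.

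The primary outcome does not use the desaturation count, so it and its sample size are unaffected.

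**What to change.** The changes concern measurement and reporting only; treatment in either arm stays as it is.

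1. Count desaturation complications in both arms from one common fixed time after randomisation or start of therapy, chosen without sight of results by arm. The hold is a minimum of 10 minutes, so a time of exactly 10 minutes may not clear it.
2. Do not start the count when SpO2 first reaches target. That conditions on a post-randomisation event and drops infants who never reach target, plausibly the sickest.
3. Report the number of infants with at least one episode, by arm.
4. Tabulate the initial period separately by arm, so that real early events stay visible.
5. Report two durations under one rule for both arms: time on device to cannula removal, and time on supplemental oxygen (FiO2 above 21% or any subnasal oxygen flow).

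The cost is outcome-definition wording. SpO2, oxygen or FiO2, and flow are already documented at each observation. If the observation times are kept with the values, the rules can also be applied to the 380 infants recruited by July 2015 without new data fields.
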